#### Interim analyses {21b}

There are no anticipated problems that are detrimental to the study participants; hence, no interim analyses will be conducted.

#### Methods for additional analyses (e.g. subgroup analyses) {20b}

There are no anticipated needs for additional analyses outside what have been described under the statistical analysis plan.

#### Methods in analysis to handle protocol non-adherence and any statistical methods to handle missing data {20c}

The intention-to-treat (ITT) method will be used to analyse data obtained from all study participants assigned to a group by randomisation. Data from study participants who complete all four cycles of SMC will be analysed using per protocol method. Participants who have only a pre- or post-intervention data will be excluded from the full analysis set.

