### Trial design {8}

A non-inferiority trial design is adopted to demonstrate that integrated SMC and anthelminthic drug delivery will be safe and tolerated among the study participants and that the incidence of the side effects will not be significantly higher in the study participants who receive the combined SMC and anthelminthic drugs than in those who receive SMC drugs alone. The study will include quantitative and qualitative components. The quantitative component will be a three-arm, observer-blind, placebo-controlled, interventional study of concurrent administration of SMC and anthelminthic drugs to pre-school and school-age children in the Saraya district of Kedougou region, southeast Senegal (Fig. 1).

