**Fig. 2 Fig2:**
[figure not shown]
Schematic diagram of the study design: A day before the commencement of the first cycle of SMC, 600 eligible children aged 1–14 years will be randomly assigned to one of three arms at a ratio of 1:1:1 to determine the safety, feasibility and tolerability of the SMC and anthelminthic drug co-administration. The first group will receive vitamin A and zinc supplement and the second group will receive praziquantel and vitamin A while the third group will receive albendazole and praziquantel. On the following day, corresponding to the start (day 1) of the first SMC cycle, all the three groups will receive amodiaquine (AQ) and sulphadoxine/pyrimethamine (SP) according to the WHO and Senegal SMC implementation guidelines. On the second and third day of the SMC cycle, all study children in the three groups will receive AQ, in line with the SMC guidelines

The qualitative component of the study will involve the conduct of structured interviews to assess the acceptability, feasibility, enablers and barriers to the combined use of anthelminthic and SMC drugs among randomly selected parents/caregivers of children enrolled in the study. Key informant interviews will also be held with SMC and MDA (anthelminthic) providers as well as with the SMC and NTD programme managers from the Senegal Ministry of Health to further explore these factors.

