### Strategies to improve adherence to interventions {11c}

Given that the side effects caused by interactions of praziquantel with albendazole are dose-dependent [22, 23] and can be reduced by taking praziquantel with carbohydrate meals [24], we will give praziquantel to the study children based on the dose recommended by WHO (40mg/kg) and we will ensure that the children take a carbohydrate-rich meal before administration of the drugs. A trained member of the research team will visit the children at home to administer the drugs in the presence of their parents/caregivers. Children who start treatment but who could not be found at home after reasonable efforts will be excluded from the study. A simple, user-friendly recording tool will be used to capture the drug administration for each child.

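### The per-protocol set rests only on completing four SMC cycles, which all arms share, and does not require the allocated day 0 drugs, the only treatment that differs between arms

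*Protocol article*

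**What the plan says.** The protocol's section on non-adherence and missing data {20c} names two analyses. The first is by randomised group: "The intention-to-treat (ITT) method will be used to analyse data obtained from all study participants assigned to a group by randomisation". The second is per protocol, with a single criterion: "Data from study participants who complete all four cycles of SMC will be analysed using per protocol method".

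The Fig. 2 legend under Trial design {8} shows what differs between arms. Before SMC starts, the groups are treated differently: "The first group will receive vitamin A and zinc supplement and the second group will receive praziquantel and vitamin A while the third group will" …; the third group's two drugs are the anthelminthics, praziquantel with albendazole. From the next day the treatment is common: "all the three groups will receive amodiaquine (AQ) and sulphadoxine/pyrimethamine (SP) according to the WHO and Senegal SMC implementation guidelines". The two days after that are also common: "On the second and third day of the SMC cycle, all study children in the three groups will receive AQ, in line with the SMC" …. Table 2 gives the same allocation, and the Discussion confirms that the anthelminthics precede the SMC drugs by a day.

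Trial design {8} sets the purpose: "A non-inferiority trial design is adopted to demonstrate that integrated SMC and anthelminthic drug delivery will be safe and tolerated". The primary outcome {12} counts adverse events over the six days following the anthelminthic dose. Under Strategies to improve adherence {11c}, staff give the drugs at home, and "A simple, user-friendly recording tool will be used to capture the drug administration for each child". The only adherence-related exclusion there is for children who start treatment and then cannot be found.

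**The concern.** A per-protocol set should separate children who received the treatment under comparison from those who did not. Here the comparison is between day 0 regimens, but the stated filter is the background treatment that every arm receives. Receipt of praziquantel, albendazole, vitamin A or zinc plays no part in it.

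This matters most in a non-inferiority safety comparison. Children in an anthelminthic arm who did not take the drugs pull that arm's adverse-event rate towards control, which favours the trial's hypothesis. A per-protocol analysis is normally run alongside intention-to-treat to check for this. A set that does not remove such children cannot serve as that check, so agreement between the two analyses would say nothing about day 0 non-receipt.

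Timing adds a second problem. The adverse-event window closes before SMC cycles 2 to 4, so requiring those cycles conditions on behaviour after the outcome. A child who reacts early and whose family then stops SMC leaves the set because of the event being measured.

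**Working it through.** **Who is in the set under the rule as written**

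| Child | Allocated day 0 drugs | SMC cycles completed | Per protocol? |
|---|---|---|---|
| A, group 3 | Not taken | 4 of 4 | Yes |
| B, group 3 | All taken | 3 of 4 (missed cycle 3) | No |
| C, group 3 | All taken, reacted, family stopped SMC | 1 of 4 | No |

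Child A was not exposed to the randomised drugs and is kept. Child B was fully exposed and is dropped. Child C had the event of interest and is dropped.

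**The plan's own figures.** The point rests on none, but the sample-size inputs are used in the third illustration below.
- Haemoglobin (difference 0.5 g/dl, SD 1.5, two-sided 5%, 90% power): n = 2 × (1.5 × (1.960 + 1.282) / 0.5)² = 189.1, which rounds up to 190 per arm against 189 stated.
- Infection prevalence (30% v 16%, pooled variance, no continuity correction): 188, as stated.

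**Illustration 1: adverse-event excess with non-receipt.** Let q be the share of an anthelminthic arm's per-protocol children who did not take the day 0 drugs. The protocol gives no value, so q and the true excess of 10 points are assumptions. Observed excess = true excess × (1 − q).
- q = 5%: 10 × 0.95 = 9.5 points
- q = 10%: 10 × 0.90 = 9.0 points
- q = 15%: 10 × 0.85 = 8.5 points

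**Illustration 2: selection on later cycles.** Assume event rates of 20% v 30%. Let a share s of children with an event then miss an SMC cycle, while all other children complete. The event rate among completers is p(1 − s) / (1 − ps).
- s = 10%: 0.18/0.98 = 18.4% and 0.27/0.97 = 27.8%, a difference of 9.5 points instead of 10
- s = 20%: 0.16/0.96 = 16.7% and 0.24/0.94 = 25.5%, a difference of 8.9 points

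Both mechanisms act in the same direction, towards similar arms.

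**Illustration 3: end-of-season outcomes with non-receipt.** The haemoglobin difference becomes 0.5 × (1 − q) with 189 per arm. The active-arm prevalence becomes 16% + q × 14 points with 188 per arm.
- q = 5%: 0.475 g/dl, power 86.8%; prevalence 16.7%, power 86.5%
- q = 10%: 0.45 g/dl, power 83.1%; prevalence 17.4%, power 82.2%

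These are two-sided comparisons, so dilution here works against finding an effect.

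**Scale.** With 200 per arm and the same assumed 20% v 30%, the 95% half-width is 1.96 × √(0.2 × 0.8/200 + 0.3 × 0.7/200) = 8.4 points. The shifts in illustrations 1 and 2, 0.5 to 1.5 points, are small beside it.

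**The case against.** - **The rule may not be exhaustive, and cycle 1 might include day 0.** Table 2 places day 0 under the cycle 1 heading, and the section on surveillance teams speaks of SMC and anthelminthic drugs as delivered in one first monthly round. The Fig. 2 legend, however, puts the randomised drugs on the day before the first cycle and makes the next day its day 1. The text is at most ambiguous, and an ambiguous set definition also needs correcting. A separate analysis plan may add detail, but the protocol does state a rule, so this is a badly fixed choice and not missing detail.
- **SMC completion is relevant.** This stands. The strategy under test is combined treatment, and end-of-season malaria and haemoglobin depend on SMC too. For those outcomes the criterion is incomplete, not wrong. A reader might infer that the set measures adherence to an irrelevant treatment; the objectives do not support that.
- **The protocol does not say that the per-protocol set applies to adverse events.** True. It does not restrict the set to other outcomes either, and the primary objective is safety, so the rule should be safe to apply there.
- **Non-receipt should be uncommon.** This stands. Staff give and record the drugs at home, and dosing falls on the day of randomisation. That limits the size but does not repair the rule.
- **Children who vomit the dose.** A reader might count them as unexposed children who dilute the comparison. The protocol collects vomiting as an adverse event {22}, so such a child contributes an event to the arm. The (1 − q) arithmetic covers only children who did not take the drugs.

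**Conclusion.** The point holds as a defect in a stated definition. The per-protocol rule filters on treatment common to all arms, does not filter on the randomised treatment and, if used for the six-day adverse-event outcome, conditions on later cycles. Each feature can bring the arms closer together in a design meant to show no important excess of side effects.

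The size cannot be estimated from the protocol and is probably small. The illustrated shifts of 0.5 to 1.5 points rest on an assumed 10-point excess, assumed non-receipt of 5% to 15% and, for the selection effect, assumed event rates of 20% v 30% with 10% to 20% of children with events missing a cycle.

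A reader might go further and infer that the trial's safety conclusion will be biased. The protocol does not support that: intention-to-treat is also planned and does not depend on this set, and supervised dosing limits non-receipt. What is lost is the value of the per-protocol analysis as a check on day 0 non-receipt.

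**What to change.** Replace the per-protocol sentence in {20c} with two definitions, applied identically in all three arms from the drug administration record already planned in {11c}:

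1. **Adverse-event outcome:** children recorded as having taken all their allocated day 0 drugs (praziquantel, albendazole, vitamin A or zinc, according to arm), with no condition on any later SMC dose. Adding the cycle 1 SMC doses may seem natural, but it would remove children who react on day 0 and then stop.
2. **End-of-season outcomes:** children recorded as having taken all their allocated day 0 drugs who also completed the four SMC cycles.

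State that a child who took the dose and then vomited stays in the safety set, with the event counted.

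The cost is a sentence or two and no new data collection. The end-of-season per-protocol set may be slightly smaller.

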### Outcomes {12}

#### Primary outcome

All solicited and unsolicited adverse events will be assessed for causal relationships to the study medications, for six consecutive days after the administration of anthelminthic drugs.

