#### Secondary outcomes

Prevalence and intensity of *Plasmodium*-helminth co-infectionFaecal egg counts for each of the four parasites (hookworm, *A. lumbricoides*, *T. trichiura*, *and S. mansoni*) and urine egg count for *S. haematobium* will be recorded, and the prevalence and arithmetic mean intensity of *Plasmodium* infection will be calculated before and after concurrent administration of SMC and anthelminthic drugs (i.e. at the end of malaria transmission season).Prevalence of anaemia and mean haemoglobin concentrationHaemoglobin concentration of all children will be checked using a HemoCue® haemoglobin analyser, before and after co-administration of SMC and anthelminthic drugs (i.e. at the end of malaria transmission season).

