#### Adverse event reporting and harms {22}

For the primary endpoint on safety and tolerability of the combined drugs, active surveillance will be used for the collection and collation of adverse drug reactions and adverse events such as vomiting, skin rash, body weakness, etc. Trained field workers, under the supervision of the investigators, will visit all enrolled children irrespective of the study arms, daily at home starting from the evening of days 0 till 3 days after completion of the first cycle of SMC course, to collect adverse events and adverse drug reactions using a purpose-designed electronic diary card. In the context of a pandemic, if travel or home visit is not possible, these follow-up visits may be done by video or telephone call. In the event that the field worker finds any grade 3 (severe) solicited symptoms, the participant will be brought to the nearest health centre or health post for examination by a study clinician.

During the field worker visits, the children’s parents/caregivers will be asked retrospectively if any medical event that might be a serious adverse event (SAE) occurred since the last visit and this information will be recorded in the diary card. Unreported SAEs detected in this way will be investigated and reported by the PI or delegate on the corresponding SAE reporting form. If a study participant is reported to be unwell at the time of a visit, the field worker will advise the parent/caregiver to report to Saraya health centre or the nearest health post, where a member of the study team will be notified for follow-up. In the event that a study participant is seriously ill, appropriate referral and transfer to the nearest referral hospital will be arranged for serious illness following review by telephone or clinical review in person.

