### Trial status

This paper is based on protocol version 2.0, dated 8 April 2022. Recruitment of the study participants will coincide with the commencement of the first cycle of SMC scheduled by the Senegal Ministry of Health for 17 June 2022. The recruitment was completed on 21 June 2022, and the follow-up of the enrolled participants will continue until 30 November 2022.

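### The analysis-set rules in {20c} and the exclusion rule in {11c} conflict with the stated ITT analysis, and none is tied to an outcome

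*Protocol article*

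**What the plan says.** Section {20c} of the protocol article gives three rules in succession and links none of them to an outcome:

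- ITT: "The intention-to-treat (ITT) method will be used to analyse data obtained from all study participants assigned to a group by randomisation".
- Per protocol: "Data from study participants who complete all four cycles of SMC will be analysed using per protocol method".
- Full analysis set: "Participants who have only a pre- or post-intervention data will be excluded from the full analysis set".

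Section {11c}, on adherence, adds a fourth: "Children who start treatment but who could not be found at home after reasonable efforts will be excluded from the study".

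The primary outcome is adverse events assessed "for six consecutive days after the administration of anthelminthic drugs". Section {22} has field workers visiting "daily at home starting from the evening of days 0 till 3 days after completion of the first cycle of SMC course". Table 2 agrees, with safety assessments from day 0 to day 6 of cycle 1. The pre- and post-intervention measurements of haemoglobin and infection belong to the secondary outcomes. The second of these is taken one month after the last SMC cycle (section {18a}). Section {20a} plans a chi-square test and a t-test at each time point, and a repeated-measures ANOVA across the two.

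**The concern.** A set that requires both a baseline and an end-of-season value is a complete-case set. Full analysis set is the usual name for the set closest to ITT, so the label and the definition pull in opposite directions. Removing children after dosing because they cannot be found is a second departure from ITT, again decided by something that happens after randomisation.

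Two things are at stake. For the secondary outcomes, post-season results are thrown away when the baseline is missing, although the planned between-arm tests at that time point do not need it. For the primary outcome, the complete-pairs rule and the four-cycle rule both turn on events long after the six-day window has closed. The trial is framed as non-inferiority on side effects. A set conditioned on staying in the study or continuing through four cycles could under-represent children who tolerated treatment badly.

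**Working it through.** **1. The rules side by side.** ITT covers all 600 randomised children. The full analysis set covers only those with both measurements. The two coincide only if nobody is lost and no sample is missing, yet the plan itself allows for 10% loss. Section {11c} takes out a further group after dosing. These rules cannot all describe the main analysis population.

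**2. Timing.** SMC cycle 1 occupies days 1 to 3, and three more days of visits end at day 6. Section {22} puts rounds one month apart, so cycle 4 falls about three months after cycle 1. The survey follows one month later, about four months after day 0. Under Trial status, "The recruitment was completed on 21 June 2022" and follow-up runs to 30 November 2022, which is 162 days later. Primary data are therefore complete months before either membership rule can be applied.

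**3. The plan's own sample sizes.** Inputs from section {14}: difference 0.5 g/dl, SD 1.5 g/dl, 90% power, two-sided 5%.

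- Haemoglobin: n = 2 × [1.5 × (1.960 + 1.282) / 0.5]² = 189.1 per arm, against 189 stated.
- Prevalence, 30% against 16%, pooled-variance formula without continuity correction: 188 per arm, against 188 stated.

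Both reproduce, so the 10% loss and 200 per arm can be taken at face value.

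**4. How many children.** 10% of 600 = 60, leaving 180 per arm. Sixty is an upper bound on children with complete first-week data who would fall outside the complete-pairs set, because some may be lost before day 6. The article gives no expected four-cycle completion rate, so the number outside the per-protocol set cannot be sized. For the secondary outcomes, the usable results lost to the complete-pairs rule are only those of children with a post-season value and no baseline.

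**5. Precision.** Going from 200 to 180 per arm at an assumed 20% event risk in both arms, the 95% half-width for a difference, 1.96 × √(2 × 0.2 × 0.8 / n), rises from 7.8 to 8.3 points. With no events in an arm, the one-sided 95% upper bound, 1 − 0.05^(1/n), rises from 1.49% to 1.65%. The effect on precision is small.

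**6. Selective loss (all rates assumed; the article gives none).** If a fraction a of children with an event and a fraction b of the others are later lost, the risk seen in the retained set is p(1 − a) / [p(1 − a) + (1 − p)(1 − b)].

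*One arm*, true risk 20%, overall loss held at 10%:

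| Loss among children with events | Observed risk |
|---|---|
| 10% | 20.0% |
| 20% | 17.8% |
| 30% | 15.6% |
| 50% | 11.1% |

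*Two arms*, true risks 20% and 30%, with a = 30% and b = 5% in both:

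- 0.14 / (0.14 + 0.76) = 15.6%
- 0.21 / (0.21 + 0.665) = 24.0%
- Risk difference: 10.0 to 8.4 points
- Risk ratio: 1.50 to 24.0 / 15.6 = 1.54
- Odds ratio: 1.71 before and after

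The implied overall loss is 10.0% in one arm and 12.5% in the other.

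*Selective loss in the combined arm only*, true risk 20% in both arms, control loss unrelated to events: 15.6% against 20.0%, a ratio of 0.78 where the truth is 1.00. The direction on a ratio scale therefore depends on the loss pattern assumed.

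**The case against.** The strongest reply is that a reader might infer that first-week safety data are discarded, and the text does not say so. No set is assigned to the primary outcome. If the ITT sentence governs safety, every day 0–6 record is kept. The pre/post language matches the paired secondary outcomes, and a treatment-related adverse event has no pre-treatment value to pair. A separate safety set may be defined in the statistical analysis plan, which is not shown; its absence from the article is not a finding. All of this stands, and it is why the safety consequence is stated conditionally.

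A reader might also infer that children with side effects are the ones removed, and that the result is tilted towards non-inferiority. Neither is established. Section {11c} gives the reason as not being found at home, nothing links loss to adverse events, and the article states no margin or scale. In the illustration with equal loss patterns, the risk ratio moves away from non-inferiority.

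On {11c}, exclusion from the study appears under adherence and does not say that collected data are deleted. That is fair, but the sentence does not say they are kept either, and taken literally it removes randomised, dosed children.

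Finally, few children should have a post-season result without a baseline, since samples are taken before dosing and willingness to give them is an inclusion criterion. Complete pairs are also what the repeated-measures ANOVA needs. That limits the size of the efficacy loss but gives no reason to apply the rule to the single-time-point tests.

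**Conclusion.** The conflict is in the stated rules and does not depend on missing detail: a complete-pairs full analysis set and the post-dosing exclusion in {11c} are both inconsistent with ITT on all randomised children. The complete-pairs rule also discards some usable post-season results, probably few.

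The effect on the primary outcome is conditional. If the complete-pairs rule were applied to it, up to 60 of 600 children with complete first-week data would be lost at the planned 10% loss. The four-cycle rule would have a similar effect of unknown size. The text does not rule out either use. The cost in precision would be small; the risk is selective loss. Should loss be related to adverse events, event risks would be understated and the risk difference could shrink, for example from 10.0 to 8.4 points under the assumed loss rates. Bias towards non-inferiority is possible but not shown.

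**What to change.** Amend the wording of {20c} and {11c}, and carry it into the analysis plan, before the data are analysed. This matters more because section {17a} leaves the analyst unmasked.

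- **Safety:** analyse all randomised children given day-0 study drug, as randomised, with all available day 0–6 data regardless of later cycles or the end-of-season visit.
- **Per protocol:** limit the four-cycle set to the efficacy outcomes.
- **Post-season outcomes:** analyse each one in all randomised children with a post-season result. Call the complete-pairs set a sensitivity set and stop calling it full.
- **Section {11c}:** reconcile it with {20c} by stating that data already collected from children who are not found remain in the ITT analysis.

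The cost is text only: no extra children, visits or samples.
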